### Ethic approval, data protection and funding

The IDrug study has been approved by the Ethics Comittees of the University of Bonn, of the Medical Association of North Rhine and of the Medical Association of Rhineland-Palatinate. It is performed according to the study protocol, ICH-GCP criteria, EU directives and applicable legal requirements. According to the Declaration of Helsinki, written consent is obtained after oral and written information. Person-identifying data, such as names and birthdays, remain at the GP-practices at all times. All data will be stored for 10 years. Patient information is pseudonymized before transfer to the Federal Institute for Drugs and Medical Devices or the Institute of Clinical Chemistry and Clinical Pharmacology. The IDrug study is financially supported by the Federal Ministry of Education and Research (BMBF). The protocol has been peer-reviewed in a strictly competitive process with several external reviewers from non-German countries evaluating the grant applications.

### Statistical analysis

#### Primary endpoint

The proportion of patients with an event (i. e. thromboembolic or bleeding event or death) will be compared between the two study arms using the Cochran-Mantel-Haenszel-Test stratified by gender and medical practice. Following the intention-to-treat principle, all randomized patients will be analyzed according to their randomized allocation. Dropouts will be counted as treatment failure in primary analysis. Risk reduction is estimated by the Mantel-Haenszel estimator of the common relative risk with the corresponding 95 % confidence interval. Additional sensitivity analyses will be performed, which include evaluation of different covariate structures.

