### Sample size

Sample size calculation was based on the primary endpoint and its primary analysis. Preceding studies reported incidence rates ranging from 8 to 10.6 % for thromboembolic and bleeding events in a population of elderly polymedicated patients on oral anticoagulants [32, 35]. Thus, for sample size calculation, we assumed an incidence rate of 10 % in the control group, which we assumed to be reduced by half as a result of the individualized risk assessment (i.e. to 5 %). To detect this anticipated difference with a power of 80 % using the Cochran-Mantel-Haenszel test (assuming equal effects in all strata), a sample size of 435 patients per arm is required. Assuming a dropout rate of 10 % about 960 patients need to be included in the study.

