### Dropout criteria

Study participation is terminated if the patient withdraws consent or if continuous data collection cannot be guaranteed (e. g. if the patient changes the GP or is absent for a long time). Discontinuation of anticoagulant/antiplatelet therapy after start of the study and receipt of the risk assessment leaflet (visit 1) does not lead to exclusion.

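### The stated 80 % power does not apply to a primary analysis that counts dropouts as failures: power is about 46 % (relative risk 0.76) if all planned dropout follows randomization, equal by arm and unrelated to events

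*Protocol article*

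**What the plan says.** All references are to the protocol article.

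- **Sample size.** The calculation is said to rest on the primary endpoint and on its primary analysis. Earlier studies gave "incidence rates ranging from 8 to 10.6 % for thromboembolic and bleeding events". From these, "we assumed an incidence rate of 10 % in the control group", with a halving to 5 % in the test arm. The power target is given as "To detect this anticipated difference with a power of 80 % using the Cochran-Mantel-Haenszel test", and "a sample size of 435 patients per arm is required". Dropout enters once, at the end: "Assuming a dropout rate of 10 % about 960 patients need to be included in the study". The caption of Fig. 1 repeats the step from 870 to 960.
- **Statistical analysis, Primary endpoint.** All randomized patients are analysed as allocated, by a Cochran-Mantel-Haenszel (CMH) test stratified by gender and practice. Then: "Dropouts will be counted as treatment failure in primary analysis". The Mantel-Haenszel relative risk is the effect estimate. The only kind of sensitivity analysis named concerns covariates.
- **Dropout criteria.** Participation ends on withdrawal of consent or "if continuous data collection cannot be guaranteed (e. g. if the patient changes the GP or is absent for a long time").
- **Study endpoints.** The primary endpoint is a thromboembolic event, a bleeding event or death within 9 months. Dropout is not part of it.

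**The concern.** Enlarging 870 to about 960 makes sense only if dropouts leave the analysis and about 435 per arm remain. The primary analysis does the opposite: dropouts stay in, and each one counts as a failure. In a comparison of proportions with an event, a failure is an event. The assumed 10 % and 5 % contain no such failures, so the section that claims to be based on the primary analysis was calculated for a different one.

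Two things are at stake. The first is power: a similar number of extra failures in both arms leaves the absolute difference slightly smaller and the variance much larger. The second is meaning: the relative risk would be read as the effect on clinical events although many counted failures may be administrative losses, such as a change of practice.

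**Working it through.** **Inputs from the article:** 10 % v 5 %; 435 per arm; about 960 in total, so 480 per arm; 10 % dropout. **Assumed:** two-sided 5 % level. The article does not state it, but it fits the 95 % confidence interval and reproduces 435.

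**1. The plan's own figure** (pooled variance under the null, mean rate 0.075):

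n = [1.96·√(2·0.075·0.925) + 0.8416·√(0.10·0.90 + 0.05·0.95)]² / 0.05² = 434.4, so 435 per arm. Power at 435 is 80.1 %. It would be 83.8 % if all 480 per arm were followed to the end. For dropout, 870/0.9 = 967 and 870 × 1.1 = 957, both about 960.

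**2. Rates under the dropout rule.** With dropout d equal in the arms and independent of events, the failure rate is p′ = d + (1 − d)·p. For d = 0.10:

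- control: 0.10 + 0.90·0.10 = 0.190
- test: 0.10 + 0.90·0.05 = 0.145
- difference 0.045; relative risk 0.145/0.190 = 0.763

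**3. Power at 480 per arm** (mean rate 0.1675):

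- null standard error √(2·0.1675·0.8325/480) = 0.02410
- alternative standard error √(0.190·0.810/480 + 0.145·0.855/480) = 0.02406
- z = (0.045 − 1.96·0.02410)/0.02406 = −0.093, so power is 46.3 %

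A power of 80 % at these rates would need 1,080 per arm. A simulation of the stratified CMH test (120 strata of 4 + 4 patients, and 80 strata of 6 + 6) gave 46 to 47 % without and about 43 % with continuity correction.

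**4. Range over assumptions**

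| Assumption | Control v test | Relative risk | Power |
|---|---|---|---|
| 10 % dropout, all after randomization | 19.0 % v 14.5 % | 0.76 | 46 % |
| 10 %, no dropout would otherwise have had an event (additive) | 20.0 % v 15.0 % | 0.75 | 53 % |
| 10 %, half lost before randomization | 14.7 % v 10.0 % | 0.68 | 58 % |
| 5 % dropout | 14.5 % v 9.75 % | 0.67 | 62 % |
| 2 % dropout | 11.8 % v 6.9 % | 0.58 | 74 % |
| 15 % dropout | 23.5 % v 19.25 % | 0.82 | 36 % |

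For the third row: 96 of 960 drop out, 48 of them before randomization. That leaves 912 randomized (456 per arm), of whom 48/912 = 5.3 % drop out later. The other rows use 480 per arm.

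**5. What is being counted.** Per 100 patients in each arm at 10 % dropout there are 19.0 + 14.5 = 33.5 failures, of which 20 are dropouts: 60 %. Leaving out dropouts who would have had an event anyway (1.0 and 0.5), 18.5/33.5 = 55 %.

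**6. Unequal dropout, illustration only.** The article gives no dropout rates by arm. With no true effect (10 % in both arms) and dropout of 12 % in control and 8 % in test, the rates are 0.12 + 0.88·0.10 = 20.8 % and 0.08 + 0.92·0.10 = 17.2 %. The chance of a significant result is then about 30 %. With the true halving and the dropout rates exchanged, the rates are 17.2 % v 16.4 %, the relative risk is 0.95 and the power is about 5 %.

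**The case against.** The best reply is that the 10 % may not all fall after randomization. It is applied to patients included in the study. By the sections on patient inclusion and on randomization, consent, blood sampling and the case report form come first, and patients are randomized only when the form arrives. Patients lost in between are not in the analysis set. If all of the 10 % were lost there, 432 per arm would remain, with power of about 80 % and a relative risk of 0.50. This stands as a limit on the size of the shortfall. It does not change its direction, because any dropout after randomization dilutes the contrast, and the article does not split the 10 %.

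A second reply is that counting dropouts as failures is an explicit, prespecified rule under intention to treat. That is fair, and keeping it is a legitimate choice. But the sample size must then include it, and it does not.

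Two stronger readings are tempting. One is that the trial simply has 46 % power; the article does not support that without the conditions above. The other is that the rule inflates the false-positive rate to 30 %. That figure comes from assumed dropout of 12 % v 8 %, which nothing in the article suggests. Patients are considered blinded, the two leaflets look alike, and a change of practice or a long absence has no stated link to the arm. The Discussion does concede that practitioners may come to recognize the arms, so imbalance is possible, but its size is unknown.

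**Conclusion.** The inconsistency is real and sits in the article itself. The stated 80 % power belongs to an analysis without dropout failures, whereas the specified primary analysis includes them.

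The figures of 46 % and 0.76 hold if the planned 10 % dropout all follows randomization, is equal between arms and is independent of events, with a two-sided 5 % level. Under the milder assumptions in the table power is 53 % to 74 %. It stays at about 80 % only if practically nobody drops out after randomization.

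At 10 % dropout, more than half of the counted failures are dropouts, and the Mantel-Haenszel relative risk does not estimate the effect on the endpoint as defined under Study endpoints. Unequal dropout could bias it in either direction, so the rule cannot be relied on to be conservative. The confirmatory test is affected, so this should be settled before the primary analysis.

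**What to change.** Reconcile the Sample size section with the primary analysis in one of two ways.

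- **(a) Change the handling of dropouts.** Let the primary analysis use each dropout's observed follow-up. Multiple imputation of the unobserved remainder keeps the CMH test and the Mantel-Haenszel relative risk. If event dates are recorded, which the article does not say, time to first event or death with censoring at dropout and a log-rank test stratified by gender and practice is the alternative. Keep dropout as failure as a sensitivity analysis. No extra patients are needed. Simulations of the log-rank option at 480 per arm, with 10 % dropout at uniformly distributed times, gave power of 0.83 unstratified, 0.84 with 80 strata and 0.80 with 160 strata. The price is the assumption that dropout is uninformative given the data, which the retained failure analysis helps to probe.
- **(b) Keep the rule.** Restate the power (about 46 % under the planned dropout) and the target relative risk (0.76), and report the result as an effect on event, death or dropout. This costs only wording, but it concedes that the trial is underpowered for its own analysis.

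Under either option, say whether the 10 % refers to losses before or after randomization.

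Collecting outcomes after a patient changes practice would reduce the problem at its source, but it is a separate, optional step and not a change of wording. Identifying data stay at the practices under the article's data protection section, so it would need new procedures and consent and data-protection arrangements.

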### Secondary endpoints

The SF-36-questionnaire for health related quality of life will be analyzed with a mixed model for repeated measurements using an unstructured covariance matrix . The mixed model contains the categorical covariates treatment, visit, gender and medical practice, a continuous covariate for the baseline SF-36-score and a treatment by visit interaction. Evaluation of drug-associated morbidity involves descriptive analysis of the number of patients with severe adverse drug reactions, the number of hospital admissions and specialist referrals due to ADR and the number of medication changes during the study period. The adherence scale will be evaluated using the non-parametric Wilcoxon-test. Survival time will be analyzed using a log-rank-test stratified by gender and medical practice. Additionally, a Cox-regression, which includes covariates treatment, gender, medical practice, age group and anticoagulant as well as a treatment by gender interaction, will be performed as a sensitivity analysis. The direct costs of the prescribed medication, unexpected GP-visits and hospitalizations will be collected and used for a cost-effectiveness analysis to compare the two study groups. In this context, two types of health outcomes will be examined. Firstly, the incidence of adverse events and secondly, the quality-adjusted-life-years (QALY) measures using the SF-36-questionnaire.

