### Follow-up and blinding

Follow-up time is 9 months for each patient. Overall, 4 visits are scheduled at intervals of 3 months. The study starts at visit 1 when the patient receives the risk assessment leaflet. During this visit, the general practitioner hands out the leaflet and explains its contents to the patient. It is at the discretion of the GP in which way and to what extent he uses the provided information for further treatment, no specifications are made. Patients are considered to be blinded to group assignment, since group assignment is not actively communicated at any time and both risk assessment leaflets have a very similar layout.

During each visit, the following information is documented in the CRF: reason for GP-consultation, vital signs, ECOG score for the patient’s physical condition [40], adverse events (bleeding events, thromboembolic events and others), number of GP-consultations in the meantime, specialist referrals, hospital admissions, sick leaves, remedies and aids and other procedures (e. g. emergency department visits, rehabilitation etc.). Data about anticoagulation/antiplatelet therapy regimen, medication and diagnoses are updated during each visit. Additionally, patients are asked to fill in questionnaires about their health related quality of life (SF-36 [33], filled in at each visit), their adherence to the medication regimen [34] (filled in at the beginning and end of the study) and their social state (filled in once at the beginning of the study).

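### The SF-36 mixed model has one baseline slope for all three follow-up visits; a baseline-by-visit term would be a nearly free refinement

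*Protocol article*

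**What the plan says.** The Secondary endpoints section of the protocol article plans a "mixed model for repeated measurements using an unstructured covariance matrix" for the SF-36. It then names the terms: "The mixed model contains the categorical covariates treatment, visit, gender and medical practice", followed by "a continuous covariate for the baseline SF-36-score and a treatment by visit interaction". Treatment by visit is the only interaction named.

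Follow-up and blinding sets the schedule: "Overall, 4 visits are scheduled at intervals of 3 months", with the SF-36 "filled in at each visit". Visit 1 is the start of the study. Taking visit 1 as baseline, this gives one baseline score and three later ones, at 3, 6 and 9 months.

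Sample size allows for 10 % dropout. Under Dropout criteria, "Study participation is terminated if the patient withdraws consent or if continuous data collection cannot be guaranteed", so later SF-36 scores of such patients are missing. Sensitivity analyses with different covariate structures are mentioned, but under the primary endpoint and not for the SF-36.

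**The concern.** The model lets the treatment effect differ by visit and leaves the residual covariance free, yet it holds the baseline slope constant over visits. A free residual covariance does not free a slope in the mean.

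If the true slope falls from month 3 to month 9, the fitted common slope lies nearer the early value, because those scores have the smaller residual variance. Month 9 is then over-adjusted for chance differences in baseline between the arms. This has two possible consequences:

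- **Precision.** The month-9 contrast is less precise than the same data allow.
- **Bias.** If the baseline-dropout relation differs between arms, the patients still observed at month 9 differ in baseline by arm. A wrong slope then corrects for that difference by the wrong amount.

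**Working it through.** **The plan's own figure.** The article states no figure for the SF-36 analysis. The sample size for the primary endpoint reproduces. For 10 % against 5 %, 80 % power and two-sided 5 % (assumed, since the section states no alpha):

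n = [1.960·√(2·0.075·0.925) + 0.842·√(0.09 + 0.0475)]² / 0.05² ≈ 434.4, so 435 per arm.

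With 960 enrolled and 10 % dropout, about 864 patients reach month 9.

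**Assumptions.** Scores have SD 1 at every visit. Correlations with baseline at 3/6/9 months are assumed in three patterns. Correlations between follow-up scores (adjacent visits; months 3 and 9) are also assumed: 0.75 and 0.70 (mild), 0.75 and 0.65 (moderate), 0.70 and 0.55 (strong). Practice and gender are left out for simplicity.

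**Precision with complete data.** Let β be the vector of true slopes and Σ the residual covariance. The fitted common slope tends to c = (1′Σ⁻¹β)/(1′Σ⁻¹1). The effect at visit t is the difference in means minus c times the difference in mean baseline, so

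variance ratio (common slope / slope by visit) = 1 + (c − βₜ)² / (1 − βₜ²).

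| Baseline correlation at 3/6/9 months | c | Month-9 calculation | Ratio, complete data | Ratio, 10 % dropout (fitted) |
|---|---|---|---|---|
| 0.70/0.65/0.60 (mild) | 0.661 | 1 + 0.061²/0.640 | 1.006 | 1.006 |
| 0.75/0.65/0.55 (moderate) | 0.689 | 1 + 0.139²/0.6975 | 1.028 | 1.030 |
| 0.80/0.60/0.45 (strong) | 0.719 | 1 + 0.269²/0.7975 | 1.091 | 1.094 |

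The last column comes from maximum-likelihood fits to 600,000 simulated patients per scenario, with dropout unrelated to baseline. A separate simulation of 1,500 trials with 435 per arm gave SDs of the month-9 effect of 0.0672 and 0.0632 when the correlation falls from 0.80 to 0.40. The ratio is (0.0672/0.0632)² = 1.13.

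The loss is concentrated at month 9. In the moderate pattern the ratios at months 3 and 6 are 1.008 and 1.003. For the effect averaged over the three visits, the ratios in the three patterns are 1.0003, 1.004 and 1.027.

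**In terms of power.** A contrast with 80 % power under slopes by visit has power Φ(2.802/√ratio − 1.960) under the common slope. With the ratios at 10 % dropout this is about 79.7 %, 78.8 % and 76.4 %.

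**Bias.** There is no true effect. The excess is the common-slope estimate minus the by-visit estimate on the same simulated data, in SD units at month 9.

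| Dropout | Mild | Moderate | Strong |
|---|---|---|---|
| 10 %, same relation in both arms (OR 0.5 per SD) | 0.0001 | −0.0003 | −0.0012 |
| 10 %, related to baseline in one arm only (OR 0.5) | 0.005 | 0.009 | 0.017 |
| 10 %, opposite directions (OR 0.5 against 2) | 0.010 | 0.021 | 0.036 |
| 20 %, opposite directions | 0.019 | 0.039 | 0.071 |

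**Scale.** The standard error at month 9 is √(4/864 · (1 − β₉²)), which is 0.054, 0.057 and 0.061 SD in the three patterns. The largest excess at 10 % dropout is therefore 0.036/0.061 ≈ 0.6 standard errors. An excess of about one standard error (0.071 against √(4/768 · 0.7975) = 0.064) needs twice the planned dropout, opposite directions and strong decay together.

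**The case against.** A main effect for baseline is a legitimate and common specification. Under randomisation it gives a consistent treatment difference unless baseline-related dropout differs by arm, and nothing in the article suggests that it will: the dropout criteria are the same for both arms and patients are regarded as blinded. The article lists the model in one sentence for one of many secondary endpoints and says what the model contains, not that it contains nothing else. On this view the term is a preference that can be left to the analysis plan.

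Much of this stands, and it limits the point to a refinement. But the article does fix the model: it names the covariance structure, every covariate and the one interaction. The suggestion changes a stated choice and does not complain of missing detail. The Discussion also concedes that GPs may come to recognise the study groups, so dropout that differs by arm cannot be excluded, although it is not shown.

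A reader might infer more than the documents support:

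- **That any baseline-related dropout biases the effect.** It does not; with the same relation in both arms the two models agree to about 0.001 SD.
- **That precision is certainly lost.** The loss vanishes if the slopes are equal, and the article gives no correlations.
- **That the loss is worth about 50 patients per arm.** That is 435·(1 − 1/1.13), and it needs the correlation to fall from 0.80 to 0.40 in six months.
- **That the common slope contradicts the unstructured covariance.** The article does not say why that structure was chosen, and the two are separate, compatible choices.
- **That month 9 is the key SF-36 result.** The article does not single it out; a month-9 contrast merely follows from the treatment-by-visit term.

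**Conclusion.** The point holds as a minor, conditional weakness of a secondary analysis. As written, one baseline slope is imposed on the 3-, 6- and 9-month SF-36 scores.

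- **Precision.** If the relation with baseline weakens over time, the month-9 variance rises by about 1 to 3 % under mild to moderate decay and by roughly 10 % or more only under strong decay. The visit-averaged effect loses much less.
- **Bias.** This also needs a baseline-dropout relation that differs between arms. It is then about 0.005 to 0.036 SD at 10 % dropout, under one standard error of about 0.06 SD.

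All these sizes rest on assumed correlations and dropout models. The direction of both effects follows from the model itself.

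**What to change.** Add a baseline-SF-36-by-visit interaction to the SF-36 model in the Secondary endpoints section, and leave all other terms and the unstructured covariance unchanged. It takes one phrase in the analysis plan and two parameters (three slopes instead of one) among roughly 870 patients. If the slopes are equal, almost nothing is lost. It is best settled before outcome data are seen, so that the term cannot look data-driven.

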**Methods/Design:**

The trial was designed as a prospective, two-arm, randomized, controlled, multicenter, pragmatic study. 960 elderly, multimorbid outpatients in general medicine are included if they take at least one high risk and one other long-term drug (polymedication). As high risk “index drugs” oral anticoagulants and antiplatelets were chosen because of their specific, objectively assessable side effects. Following randomization, test group patients receive an individualized risk assessment leaflet evaluating their personal data concerning bleeding- and thromboembolic-risk-scores, potential drug-drug-interactions, age, renal function and pharmacogenetic factors. Control group patients obtain a standardized leaflet only containing general information on these criteria. Follow-up period is 9 months for each patient. Primary endpoint is the occurrence of a thromboembolic/bleeding event or death. Secondary endpoints are other adverse drug reactions, hospital admissions, specialist referrals and medication changes due to adverse drug reactions, the patients’ adherence to medication regimen as well as health related quality of life, mortality and resulting costs.

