### Study endpoints

Primary endpoint is the occurrence of a thromboembolic or bleeding event or death within a 9 months study period. Secondary endpoints are the occurrence of other ADR, the number of hospital admissions due to ADR, the number of specialist referrals due to ADR, the number of medication changes, the patients’ adherence to the medication regimen, time to death, health-related quality of life, costs of medication and of additional general practitioner (GP) consultations and hospital treatments as well as a cost-benefit analysis.

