### Risk assessment

Both risk assessment leaflets contain general information on risk factors for adverse drug reactions. However, the individualized leaflet also includes an additional personalized risk evaluation which takes the patients clinical data into account. For test group patients, their individual HAS-BLED- and CHA2DS2-VASc-Scores are calculated. The current medication is checked for potential drug-drug-interactions and it is checked whether dose adjustments related to the patients’ kidney function would apply, using two independent validated evidence-based clinical decision support systems, AiDKlinik® [38] and the ABDA database [39]. Furthermore, the patients’ genetic profiles for *CYP2C9*, *CYP2C19* and *VKORC1* are matched with their medication to check for potential drug-gene-interactions according to their genotypes. References are the guidelines published by the Royal Dutch Pharmacists Association - Pharmacogenetics Working Group [19] and the Clinical Pharmacogenetics Implementation Consortium (CPIC) [20]. The standardized leaflet, however, only contains general information about these risk factors for adverse drug reactions.

The leaflets have a short and clearly arranged design in order to be implementable in everyday practice. They only contain clinically relevant information. Additionally, they are written in a generally understandable manner, so that they can be read easily by doctors as well as patients. A scheme of the risk assessment leaflets is displayed in Fig. 2.

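### All medication changes are counted as drug-associated morbidity, although the abstract limits them to ADR-caused changes and the leaflet can itself prompt changes; separately, the endpoint of other ADR is analysed only for severe ADR

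*Protocol article*

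**What the plan says.** Three places in the protocol article describe these secondary endpoints.

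- **Abstract, Methods/Design:** the list of secondary endpoints includes "medication changes due to adverse drug reactions". It also names other ADR, without a severity limit.
- **Study endpoints:** "Secondary endpoints are the occurrence of other ADR", again with no severity limit. Admissions and referrals are each tied to ADR. The list then continues with "the number of medication changes, the patients’ adherence to the medication regimen", where the tie to ADR is absent.
- **Statistical analysis, Secondary endpoints:** "Evaluation of drug-associated morbidity involves descriptive analysis" of several measures. The first is the number of patients with severe ADR. The others are "the number of hospital admissions and specialist referrals due to ADR and the number of medication changes during the study period".

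Two other sections bear on how a medication change should be read. Under Risk assessment, the current medication of test-arm patients is screened for interactions and matched with their genotypes, and "it is checked whether dose adjustments related to the patients’ kidney function would apply". Under Follow-up and blinding, "It is at the discretion of the GP in which way and to what extent he uses the provided information for further treatment".

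**The concern.** There are two separate problems.

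First, the endpoint for medication changes is stated in two ways, and the wider one is the one analysed under a morbidity label. The Background gives the aim as testing whether individualising drug therapy improves safety and efficacy. A GP who acts on an interaction, renal or genotype finding will often do so by altering a prescription. Such a change is a sign that the intervention was taken up. A change made because the patient suffered an ADR is a sign of harm. One count that mixes the two has no clear direction, and the mixture is likely to differ between arms because only the test arm gets patient-specific findings.

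Second, the first-listed secondary endpoint, other ADR of any severity, has no matching analysis in the article. What is analysed is the narrower set of severe ADR. The stated study aim is the effect on ADR, so the wider endpoint matters to the reader.

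**Working it through.** **Figures in the plan.** The protocol gives no rate for medication changes or for other ADR, so there is no figure on this point to reproduce. Its only quantitative basis is the primary endpoint. With 10 % against 5 %, 80 % power and a two-sided 5 % level (my assumption; the level is not stated), the pooled two-proportion formula gives

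n = [1.96·√(2·0.075·0.925) + 0.842·√(0.10·0.90 + 0.05·0.95)]² / 0.05² ≈ 435 per arm,

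which matches the plan. Nothing below affects it.

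**Comparison of the texts.**

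| Measure | Abstract | Study endpoints | Statistical analysis |
|---|---|---|---|
| Admissions, referrals | due to ADR | due to ADR | due to ADR |
| Medication changes | due to ADR | unrestricted | unrestricted, under morbidity |
| ADR | other ADR | other ADR | severe ADR only |

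In the abstract the qualifier directly follows medication changes, so it covers them on any reading of the list. The two later sections both attach it to admissions and referrals and both leave it off medication changes.

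**Can the total point the wrong way?** Define, per patient over follow-up:

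- a = ADR-caused changes in the control arm (assumed 0.1 to 0.5);
- a/2 = ADR-caused changes in the test arm (assumed halving, a favourable leaflet effect);
- b = background changes for other reasons, equal in both arms (assumed 0.5 or 1.0);
- e = leaflet-prompted changes in the test arm in excess of those in the control arm (assumed).

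The test-to-control ratio of total counts is

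R = (b + a/2 + e) / (b + a).

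R exceeds 1 exactly when e > a/2. The threshold does not depend on b; b only moves R towards 1.

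| a | threshold a/2 | R at e = 0, b = 1.0 | R at e = 0.25, b = 0.5 | R at e = 0.25, b = 1.0 |
|---|---|---|---|---|
| 0.1 | 0.05 | 0.955 | 1.333 | 1.182 |
| 0.2 | 0.10 | 0.917 | 1.214 | 1.125 |
| 0.3 | 0.15 | 0.885 | 1.125 | 1.077 |
| 0.5 | 0.25 | 0.833 | 1.000 | 1.000 |

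For example, with a = 0.2, b = 1.0 and e = 0.25, R = (1.0 + 0.1 + 0.25)/(1.0 + 0.2) = 1.35/1.2 = 1.125, although ADR-caused changes fell by half. With 960/2 = 480 patients per arm, thresholds of 0.05 to 0.25 correspond to 0.05 × 480 = 24 to 0.25 × 480 = 120 extra changes in the test arm.

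**The ADR endpoint.** No arithmetic applies. The analysis is a "descriptive analysis of the number of patients with severe adverse drug reactions", a subset of the endpoint as defined. The cost-effectiveness analysis uses the incidence of adverse events as a health outcome. That is a different measure and does not supply the missing analysis of other ADR.

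**The case against.** The case on the other side is substantial, and much of it stands.

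- **No harm rule.** A reader might infer that a successful leaflet would be reported as increasing morbidity. The document does not go that far. The measures are listed separately and described, with no composite, no test and no rule that more changes mean harm, and Study endpoints lists medication changes neutrally. What remains is that the morbidity label does not fit an unrestricted count.
- **Size.** A reader might infer a doubling of the count. That needs background changes to be left out. With 480 patients per arm, 144 ADR-caused changes per arm and 144 leaflet-prompted changes, the ratio is (144 + 144)/144 = 2.0. Adding an assumed 480 background changes per arm gives (480 + 144 + 144)/(480 + 144) = 1.23. If the leaflet also halves ADR-caused changes, it is (480 + 72 + 144)/624 = 1.12. Every input is assumed.
- **Test arm only.** This would be too strong. Control patients and their GPs also receive general information on the same risk factors, randomisation is within practice, and each GP sees both leaflets. Use of the leaflet is at the GP's discretion. More changes in the test arm are an expectation drawn from its content, not something the protocol specifies.
- **Attribution.** Limiting the count to ADR-caused changes requires a judgement by GPs who, as the Discussion concedes, may come to recognise the arms. A total count is less exposed to that bias. This is a good reason to keep the total as well, but not to call it morbidity.
- **Description only.** Describing secondary endpoints is legitimate, and detailed models are commonly left to an analysis plan that is not shown. The absence of a between-arm model is not an error.
- **The ADR aim.** A reader might infer that the aim goes unanswered. It does not: bleeding and thromboembolic events are in the primary endpoint, with a stratified test, relative risk and 95 % confidence interval.

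**Conclusion.** The concern holds in a limited form. The abstract conflicts with the two later sections on whether medication changes must be due to ADR, and the wider count stands under a morbidity label. As written, that count cannot be interpreted as morbidity, because it pools ADR-caused changes with changes the leaflet may prompt. Its direction can reverse once the excess of leaflet-prompted changes passes a/2 per patient, which is 0.05 to 0.25 for a between 0.1 and 0.5. This rests on an assumed halving of ADR-caused changes and equal background rates. The documents allow no estimate of how likely a reversal is.

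The step from other ADR to severe ADR is a separate mismatch between definition and analysis. It might be taken as a second source of a wrong-way result, but a severity limit alone reverses nothing; it leaves the defined endpoint without its analysis.

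Both matters concern descriptive secondary endpoints. They should be corrected, but they leave the primary analysis and the sample size untouched.

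**What to change.** 1. Reconcile the abstract, Study endpoints and the statistical section so that each states the same medication-change endpoint.
2. Report medication changes due to ADR as the morbidity measure. Report all changes, or those for other reasons, separately as a process measure of how far the leaflet was used. Keep the total in any case, because attribution may be influenced by knowledge of the arm.
3. Record a reason for each change at the existing visits, where medication is already updated. The case report form is not shown, so first check whether it already captures this.
4. Report the number of patients with any other ADR by arm, with severe ADR as a subset. A between-arm estimate with a 95 % confidence interval would be preferable but is optional.

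The cost is some rewording, one reason code per change if none exists, and a few more table rows. The main drawback is the GP's attribution of cause, which keeping the total count offsets in part. No extra visits or patients are needed.
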